## Methods/design

The trial is a phase III, double-blind, parallel-group, 1 to 1 randomised, placebo-controlled, multicentre clinical superiority trial of orally administered co-trimoxazole versus placebo in patients with moderate to severe (FVC ≤ 75% predicted) IPF, with outcomes assessed over a median treatment period of 27 (range 12–42) months. Participants receive co-trimoxazole or placebo until they meet a primary endpoint event, they withdraw consent, or the trial concludes. This trial is designed to align with routine care as much as possible and the trial visits are intended to coincide with routine clinical follow-up visits. Follow-up of assessment measures will continue for the duration of the trial for those participants stopping trial medication due to adverse events or patient choice. The vital status and details of admission to hospital will be captured for all patients who have consented to participate in the trial regardless whether they have withdrawn from the intervention or trial assessments.

Figure 1 provides a study flowchart of the trial design and Fig. 2 provides the time and event schedule. The trial protocol (v3.0, dated 16 May 2016) is based on the Standard Protocol Items: Recommendations for Interventional Trials (SPIRIT) 2013 Statement for protocols of clinical trials (see Additional file 1).

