### Secondary outcomes

The individual components of the primary outcome: time to death (all causes) or transplant and time to first non-elective hospital admission will be analysed separately as secondary outcomes. In addition, respiratory-related events will be analysed separately from non-respiratory-related events. The following measurements will also be undertaken at baseline, 3 and 6 months post randomisation, then 6-monthly for the duration of the trial plus at the end of trial/hospitalisation.

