### Safety outcomes

Blood for full and differential white cell counts, urea and electrolyte assays and liver function assessment is being taken at baseline, 6 weeks, 3, 6, 9 and 12 months then 6-monthly for the duration of the trial and at the end of trial/hospitalisation. The 6-week and 9-month blood tests may be taken in primary care, with assessment of adverse events being captured by phone.

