### Statistical analysis

All analyses will be conducted according to a detailed statistical analysis plan. Analyses will be adjusted for site and the use of baseline, licensed medication for IPF. The analysis populations are defined as intention-to-treat (all randomised individuals regardless of adherence), per-protocol (all randomised individuals who adhere to the trial medication to within 80% (based on pill counts)), modified-per-protocol (all randomised individuals who adhere to the high-dose regimen) and safety population (all patients randomised who received at least one dose of the trial treatment). Non-compliance will be dealt with using a Compliance-Adjusted-Causal-Effect (CACE) analysis, using compliance data from returned medication (pill counts).

The primary outcome will be analysed using a Cox proportional hazards model adjusted for the variables included in the minimisation algorithm (baseline licensed IPF medication and site). The results will be presented as the Kaplan-Meier estimate of the survival function for each treatment arm separately and, if appropriate, the median will be estimated. The treatment effect size will be the hazard ratio and estimated with 95% confidence intervals and *p* values.

At each relevant time point from 6 weeks post randomisation, the K-BILD, EQ5D, LCQ, spirometry (FVC per cent predicted, FEV per cent predicted, FVC absolute value, FEV absolute value and FVC/FEV ratio) and DLCO will be analysed using linear model to compare the average values between the treatment arms adjusted for the variables included in the minimisation algorithm: baseline disease-modifying therapy and site will be included as a random effect. The effect size will be the mean difference and will be presented with 95% confidence intervals and *p* values.

The MRC Breathlessness Score and cough score will be analysed using a Mann-Whitney test to compare the distribution of the score between the treatment arms. A generalised effect size will be estimated and presented with 95% confidence intervals and *p* values.

The safety analysis will be based on the pre-defined population (as above). Summary tables will be presented for incidence rates (number of patients with at least one incidence) of adverse events and serious adverse events coded according to the Medical Dictionary for Regulatory Activities (MedDRA). Tables of change from baseline will be presented for the blood and other clinical laboratory assessments.

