### Mechanistic analysis

Analysis of the biomarkers from stored blood will be performed using the same linear mixed model as for the analysis of K-BILD. Analysis of routine microbiology and 16S ribosomal ribonucleic acid (rRNA) sequence data will be descriptive by tabulating the different types of microbiological cultures and their relative prevalence or signal strength.

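### Continuous secondary outcomes are compared visit by visit without using the baseline value or the patient's other visits, from a 6-week start at which they are not measured

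*Protocol article*

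**What the plan says.** **Model.** The Statistical analysis section of the protocol article takes K-BILD, EQ5D, LCQ, five spirometry measures and DLCO. "At each relevant time point from 6 weeks post randomisation", these "will be analysed using linear model to compare the average values between the treatment arms". Adjustment is for the minimisation variables: "baseline disease-modifying therapy and site will be included as a random effect". Read literally, that clause could make both terms random, but site is the only plausible random effect. For reporting, "The effect size will be the mean difference and will be presented with 95% confidence intervals and *p* values". No term is named for the outcome's baseline value, for the patient or for time.

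**Related label.** The Mechanistic analysis section says that the biomarkers will be analysed "using the same linear mixed model as for the analysis of K-BILD".

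**Schedule.** The Secondary outcomes section places the measurements at baseline, 3 and 6 months, "then 6-monthly for the duration of the trial plus at the end of trial/hospitalisation". Week 6 appears under Safety outcomes: "The 6-week and 9-month blood tests may be taken in primary care", with adverse events taken by phone.

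**Follow-up after stopping drug.** Methods/design ends trial treatment at a primary endpoint event, withdrawal of consent or the end of the trial. It continues assessments "for those participants stopping trial medication due to adverse events or patient choice". It does not say whether questionnaires and lung function continue after a primary event.

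**The concern.** Three features of the stated method deserve attention.

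- **Unused data.** Each visit is compared on its own. The baseline value, usually the best predictor of a later score, and the patient's intermediate values are set aside although they will have been collected. This costs precision.
- **Outcome-dependent loss.** In moderate to severe IPF, patients leave assessment because they are ill. A visit-wise model without the patient's earlier values cannot allow for a sick patient having dropped out of a later visit. If control loses more such patients, the patients who remain in control look healthier and a benefit of co-trimoxazole on quality of life or lung function is understated.
- **Start point.** The analysis text starts at a contact where none of these outcomes is scheduled.

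**Working it through.** **Inputs.** From Sample size: medians of 28.8 months (control) and 51.1 months (co-trimoxazole), 96 events, 80% power, two-sided 5%, 30 months' recruitment plus 12 months' follow-up. From Methods/design: 330 patients, 1:1, so 165 per arm. From Health-related quality of life: K-BILD SD 26, important difference 8.

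**Step 1: reproduce the plan's figure.** The hazard ratio is 28.8/51.1 = 0.5636. Schoenfeld's formula gives 4 × (1.960 + 0.842)² / (ln 0.5636)² = 31.4/0.329, which rounds up to 96 events. Power at 96 events is 80.2%. The plan's figure reproduces, so its medians are a fair basis for what follows.

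**Step 2: event-free share.** Under exponential times, S(t) = exp(−ln 2 × t / median). With uniform recruitment, the share of patients who can have reached visit t is 1 up to 12 months and (42 − t)/30 after that. Expected numbers per arm are 165 × reach × S(t).

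| Month | Control S | Co-trimoxazole S | Gap | Reach | Number, control vs co-trimoxazole |
|---|---|---|---|---|---|
| 3 | 0.930 | 0.960 | 0.030 | 1.00 | 154 vs 158 |
| 6 | 0.866 | 0.922 | 0.056 | 1.00 | 143 vs 152 |
| 12 | 0.749 | 0.850 | 0.101 | 1.00 | 124 vs 140 |
| 24 | 0.561 | 0.722 | 0.161 | 0.60 | 56 vs 71 |
| 36 | 0.420 | 0.614 | 0.193 | 0.20 | 14 vs 20 |

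The counts are those contributing at each visit only if assessment ends at the primary event.

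**Step 3: possible bias.** Let patients who have had an event score g units lower than those who have not, with no true treatment effect on the score. The event-free mean in an arm exceeds that arm's overall mean by (1 − S) × g. The difference between arms, co-trimoxazole minus control, is then −(S for co-trimoxazole − S for control) × g. The documents give no value for g. Assume 8 to 16 units:

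- 12 months: −0.101 × 8 = −0.8; −0.101 × 16 = −1.6
- 24 months: −0.161 × 8 = −1.3; −0.161 × 16 = −2.6

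A simulation gives the same direction. It used one million patients per arm, a standard normal latent score, no treatment effect on the score, and hazards set to the two medians. If the log-hazard falls by 0, 0.5 or 1.0 per SD of the score (assumed), the bias in K-BILD units at SD 26 is about 0, −1.6 or −2.7 at 12 months, 0, −2.9 or −3.8 at 24, and 0, −3.9 or −4.6 at 36. If the drug has no effect on the primary event, the two S(t) curves coincide and this bias is zero.

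**Step 4: precision.** The 95% half-width without baseline adjustment is 1.96 × 26 × √(1/n₁ + 1/n₂).

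- 24 months: 1.96 × 26 × √(1/56 + 1/71) = 9.1 units
- 36 months: 1.96 × 26 × √(1/14 + 1/20) = 17.8 units

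Both exceed the 8-unit important difference. Adjusting for a baseline value with correlation ρ to the follow-up score multiplies the half-width by about √(1 − ρ²). The documents give no ρ.

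**Step 5: timing.** The Secondary outcomes section has no 6-week measurement, and Safety outcomes gives week 6 to bloods and adverse events. The first post-baseline visit with these outcomes is 3 months.

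**The case against.** Several stronger readings are tempting, and the document does not support them.

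- **That the later comparisons are distorted.** The article never says that they are confined to patients still attending. It defines an intention-to-treat population of all randomised patients, keeps assessing those who stop for adverse events or by choice, and is silent, not negative, on assessment after a primary event. The wording on the end-of-trial or hospitalisation measurement is ambiguous. The bias needs three conditions together: assessment ending at the event, a drug effect on events, and a link between event risk and score. Even then it is well below the important difference and runs against co-trimoxazole, so this mechanism does not favour a false claim of benefit.
- **That staggered entry selects patients differently by arm.** It does not. It thins both arms equally and costs only precision.
- **That no time point leads and there are too many tests.** Nine listed measures at seven visits give 63 p values, or 56 without LCQ, which no schedule collects. The headline time point and multiplicity rules may properly sit in the analysis plan, which is not shown.
- **That admission values are mixed with routine ones.** Nothing says so, and their handling is also matter for the analysis plan.

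The best defence of the method itself is the linear mixed model label under Mechanistic analysis: the visit comparisons might be contrasts from one longitudinal model. However, site is the only plausible random effect in the description, and a site effect does not link a patient's visits. The defence therefore fails on the text. The word *relevant* softens the 6-week start. As no data exist then, no result would change, but the inconsistency remains.

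It is also true that a mixed model assumes data missing at random and implicitly carries on beyond death. It weakens the missingness assumption; it does not remove the problem.

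**Conclusion.** The point holds as an improvement to a method that the article does fix. As described, the model discards the outcome's baseline value and the patient's other visits, and it starts from a time with no such data.

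On the design's own medians, and if assessment ends at the primary event, the event-free share differs between arms by 10 percentage points at 12 months and 16 at 24. The resulting bias is conditional and modest: about 1.3 to 2.6 K-BILD units against co-trimoxazole at 24 months on an assumed 8 to 16 unit gap, and up to 3.8 in the simulation. It is zero if the drug does not affect events or if event risk is unrelated to the score. The loss of precision depends only on the numbers remaining: half-widths of about 9 units at 24 months and 18 at 36 if patients leave assessment at the event, and smaller if they stay. Certain distortion is not established.

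**What to change.** In the Statistical analysis section, replace the visit-wise linear model with one repeated-measures mixed model per continuous outcome. It should use all scheduled visits from 3 months, with treatment by visit, baseline value by visit, baseline IPF medication, random site and within-patient correlation. Report the mean difference at each visit from that model. Change the start from 6 weeks to 3 months, to agree with Secondary outcomes and Safety outcomes. Mechanistic analysis refers to the same model, so the change carries over to the biomarkers at their own sampling times.

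The cost is wording and a standard model, with no new data, and the article leaves the full details open until database lock. The small downside is the reliance on missing at random: the model does not by itself resolve truncation by death, so a sensitivity analysis for loss after the primary event remains useful. Its form, the headline time point and the handling of admission assessments can be left to the analysis plan.

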### Identification, recruitment and randomisation

The main method of patient identification is by review of ILD MDT meeting minutes or summaries, but is also via screening patient registries, hospital medical records and databases of research-interested patients. Potential recruits are being approached by local clinic teams and provided with a patient information sheet and given at least 24 h to read this prior to consent. Consent is taken by appropriately-trained clinicians or delegated members of staff. All patients are invited to provide additional consent to provide a sample of blood for deoxyribonucleic acid (DNA) analysis; however, this is optional and patients can refuse whilst remaining eligible for the main trial.

Following consent, patients meeting all inclusion criteria and none of the exclusion criteria (after review of their screening bloods) may be randomised without a subsequent visit. Randomisation is performed centrally according to a computer-generated randomisation code with the treatment group allocation sent to research pharmacists only. Minimisation factors are: research site and the use of baseline licensed medication for IPF.

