### Health-related quality of life

This is being assessed in a number of ways: (1) the King’s Brief Interstitial Lung Disease (K-BILD) health-related quality of life questionnaire [21] which is the only validated ILD-specific instrument. This 15-question, self-completed patient questionnaire has a mean score of 53 (standard deviation 26) units in IPF and a minimum clinical significant difference of 8 units; (2) the MRC Breathlessness Score [16] which is the most widely utilised dyspnoea score for patients with ILD; (3) the EuroQol 5-dimension (EQ5D) questionnaire [22] will be used to determine quality-adjusted life years (QALYs) but a cost-utility analysis will not be undertaken. The K-BILD does not specifically capture cough so we are assessing cough using a Visual Analogue Scale. Overall, quality of life is being captured using a 6-point Likert global rating of concept scale.

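### The stated model for K-BILD, EQ5D, spirometry, DLCO and the blood biomarkers omits the outcome's baseline value, although it is collected; this costs precision, not validity

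*Protocol article*

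**What the plan says.** The protocol article, under Statistical analysis, sets one model for K-BILD, EQ5D, LCQ, spirometry and DLCO.

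- **Timing:** the comparison is made "At each relevant time point from 6 weeks post randomisation", so baseline is not one of the analysed responses.
- **Model:** the outcomes "will be analysed using linear model to compare the average values between the treatment arms adjusted for the variables included in the minimisation algorithm". The sentence then names disease-modifying therapy at baseline, and site as a random effect.
- **Effect measure:** "The effect size will be the mean difference and will be presented with 95% confidence intervals". The outcome is not defined as change from baseline.

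The section on identification, recruitment and randomisation confirms the covariate list: "Minimisation factors are: research site and the use of baseline licensed medication for IPF". No baseline outcome is minimised on.

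Mechanistic analysis extends the model: "Analysis of the biomarkers from stored blood will be performed using the same linear mixed model as for the analysis of K-BILD".

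Baseline data are scheduled. Secondary outcomes says "The following measurements will also be undertaken at baseline, 3 and 6 months post randomisation", and this covers the quality-of-life and lung-function sections that follow. Peripheral blood lists baseline among its sampling times. For K-BILD the article states that the instrument "has a mean score of 53 (standard deviation 26) units in IPF and a minimum clinical significant difference of 8 units".

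**The concern.** For a continuous outcome measured before and after randomisation, the baseline value is usually among the strongest predictors of the later value. A model that leaves it out keeps between-patient variation in the residual that could have been removed. The word baseline does appear in the covariate list, but it describes the IPF therapy, not the outcome.

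The omission sits oddly with the rest of the article. Patient characteristics requires a stable IPF regimen before screening so that baseline values are representative. It also excludes recent respiratory infection because reliable baseline lung function would be hard to obtain. The efficacy model then does not use those baselines. Change from baseline appears only in the safety laboratory tables.

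At stake is the width of the confidence intervals for the secondary and mechanistic outcomes, and with it the chance of detecting a K-BILD difference that the article itself calls clinically significant.

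**Working it through.** **The plan's own figure.** The article states no power or precision for the secondary outcomes. Its only power figure is for the primary outcome. That figure reproduces: HR = 28.8/51.1 = 0.5636, and 4 × (1.96 + 0.842)² / (ln 0.5636)² = 95.5, so 96 events for 80% power. Nothing below depends on it.

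**Inputs from the article**
- K-BILD SD 26 and difference 8 (Health-related quality of life).
- 330 patients randomised 1:1, so 165 per arm; Sample size works with 264, so 132 per arm.
- Two-sided 5% level.

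**Assumptions, not in the article**
- rho, the baseline to follow-up correlation after allowing for therapy and site: 0.3, 0.5 and 0.7.
- About 100 per arm assessed, as a scenario with attrition. As a guide, the planning medians give 12-month event-free shares of 2^(−12/28.8) = 0.749 and 2^(−12/51.1) = 0.850. With 20% loss (assumed), 165 × 0.8 × 0.749 ≈ 99 and 165 × 0.8 × 0.850 ≈ 112 patients remain.
- SD 26 applies at follow-up. Any variance explained by therapy and site is ignored.

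**Formulas**
- Without baseline: SE = 26 × √(2/n).
- With baseline as covariate: SE = 26 × √(1 − rho²) × √(2/n).
- Power = Φ(8/SE − 1.96).

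**Variance ratio, 1 − rho²:** 0.91, 0.75 and 0.51 at rho 0.3, 0.5 and 0.7, a saving of 9%, 25% and 49%.

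**165 per arm, in full**
- No baseline: SE = 26 × √(2/165) = 2.86; 95% CI half-width 5.6; power Φ(2.79 − 1.96) = 79.8%.
- rho 0.3: SE 2.73; half-width 5.4; power 83.4%.
- rho 0.5: SE 2.48; half-width 4.9; power 89.7%.
- rho 0.7: SE 2.04; half-width 4.0; power 97.5%.

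**Power to detect 8 K-BILD units**

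| Per arm | No baseline | rho 0.3 | rho 0.5 | rho 0.7 |
|---|---|---|---|---|
| 165 | 79.8% | 83.4% | 89.7% | 97.5% |
| 132 | 70.5% | 74.6% | 82.3% | 93.8% |
| 100 (assumed) | 58.5% | 62.6% | 71.0% | 86.1% |

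At rho 0.7, 165 per arm with adjustment carry as much information as 165/0.51 ≈ 324 per arm without it.

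**The case against.** **The detail belongs to the analysis plan.** The article condenses a longer document and defers full details to an analysis plan to be finalised before database lock. Its covariate sentence does not say that nothing else will be added. This stands in part: the final analysis may well include baseline, and the article cannot show that it does not. But the article is not silent. It names the outcomes, the model, the effect measure and the covariates. A plan that follows it inherits the omission, and one that adds baseline changes a published model.

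**The model is valid.** This stands. A reader might infer that chance baseline differences will be mistaken for treatment effects. They will not be, in any systematic sense: under randomisation the comparison is unbiased, and its confidence interval and type I error already allow for chance imbalance. The loss is in precision.

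**The gain rests on a correlation that the article does not give.** This also stands. At rho 0.3 the saving is only 9%. The K-BILD SD is quoted for IPF in general, while the trial restricts entry by FVC and dyspnoea, so both SD and rho may differ here. The 100-per-arm row is one scenario; the 3- and 6-month visits would retain more patients.

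**Not every outcome has a documented baseline.** Correct. For neutrophil elastase the Discussion names only the end of the trial, no timing is given for PIIINP, and LCQ is in the model list but not described among the measurements.

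**Scale of the biomarkers.** A reader might also infer that the biomarkers will be analysed untransformed, with a further loss of efficiency. Mechanistic analysis states no scale, and the article gives no biomarker distribution from which to size such a loss, so that inference is unsupported.

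**Conclusion.** The point holds as a matter of precision. The stated model for K-BILD, EQ5D, spirometry and DLCO, and by extension the blood biomarkers, adjusts for IPF medication and site and leaves out a baseline value that is collected. The cost is modest at rho 0.3 and substantial from about 0.5 upwards: on the article's own K-BILD figures at full sample size, power of about 80% could be about 90% at rho 0.5. The size depends on the assumed rho, on SD 26 holding in this population, and on the number still assessed.

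The change should be made, but the trial's main conclusion does not hang on it. Only secondary and mechanistic outcomes are affected. The primary Cox analysis is untouched, and so are the MRC and cough scores, which have a separate rank-based analysis.

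**What to change.** In the analysis plan, before unblinding, add the baseline value of the same outcome as a covariate in each continuous secondary and biomarker model wherever a baseline measurement exists, alongside IPF medication and site. Each spirometry measure should take its own baseline. For neutrophil elastase, PIIINP and LCQ, first confirm whether a baseline value is available, and say so where it is not.

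If the analysis plan already contains this, it is enough to record that it extends the model in the article. The cost is a change of wording: no extra data, visits or patients are needed. Timing matters, because a covariate added after unblinding would look data-driven.

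### The MRC breathlessness and cough scores get an unadjusted Mann-Whitney test, against the protocol's own adjustment rule and without their baseline values; the linear-model list also names an undefined LCQ

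*Protocol article*

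**What the plan says.** All places are in the protocol article.

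- **General rule (Statistical analysis, first paragraph).** "Analyses will be adjusted for site and the use of baseline, licensed medication for IPF". No exception is stated. These are the two factors used in allocation (Identification, recruitment and randomisation): "Minimisation factors are: research site and the use of baseline licensed medication for IPF".
- **Models that follow the rule.** The Cox model for the primary outcome repeats the adjustment. So does the linear model for K-BILD, EQ5D, lung function and others: "adjusted for the variables included in the minimisation algorithm: baseline disease-modifying therapy and site will be included as a random effect".
- **MRC and cough.** "The MRC Breathlessness Score and cough score will be analysed using a Mann-Whitney test to compare the distribution of the score". The result is to be summarised so: "A generalised effect size will be estimated and presented with 95% confidence intervals and" p values. No covariate or stratum is named.
- **Baseline values.** The Secondary outcomes section schedules these measurements at baseline, 3 and 6 months, and then every 6 months.
- **LCQ.** The linear-model paragraph begins: "At each relevant time point from 6 weeks post randomisation, the K-BILD, EQ5D, LCQ, spirometry". The Health-related quality of life section gives the cough measure: K-BILD does not capture cough specifically, "so we are assessing cough using a Visual Analogue Scale".

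**The concern.** There are two faults of specification.

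First, the general rule and the MRC and cough paragraph cannot both hold as written. A two-sample Mann-Whitney test takes no covariates, so these two outcomes are analysed without the minimisation factors although the section says that analyses are adjusted for them. The test also leaves unused the baseline score of the same measure, which is often the strongest predictor of a patient-reported score. Two patient-reported secondary outcomes are therefore estimated less precisely than the collected data allow.

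Second, the linear-model list names an LCQ that has no counterpart in the outcome sections, while the cough measure that is described, the Visual Analogue Scale, is not named in the analysis section. A reader has to assume that the cough score there is that scale, and cannot tell what the LCQ is or when it is measured.

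**Working it through.** **1. Text comparison: adjustment**

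| Outcome | Method fixed | Site and IPF medication | Baseline value of the outcome |
|---|---|---|---|
| Primary composite | Cox model | yes | not applicable |
| K-BILD, EQ5D, lung function | linear model | yes, site as random effect | not named |
| MRC, cough | Mann-Whitney | none named | none named |

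Of the three methods fixed for comparing the arms, only the third departs from the general rule.

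**2. Text comparison: LCQ**

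In the text shown, LCQ occurs once, in the linear-model paragraph. It is absent from the abstract's outcomes, the objectives at the end of the Background (which speak of a cough score), the Health-related quality of life section and the Abbreviations, and it is never expanded.

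**3. Effect of breaking the stated rule (site and medication only)**

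The documents give no figure to reproduce, so this is an illustration. From the document: 330 patients randomised. Assumed: 20 sites, a 5-level score, a latent shift of 0.33 SD, arms balanced within site-by-medication strata, two-sided 5%, 4,000 runs per setting. The comparison is a plain Mann-Whitney test against a rank test stratified by site and medication (van Elteren).

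| Prognostic strength of the factors | Type I error, plain / stratified | Power, plain / stratified | Change in power |
|---|---|---|---|
| none | 4.6% / 4.7% | 81% / 79% | −2 points |
| site variance share 0.05, medication shift 0.3 SD | 4.7% / 5.8% | 80% / 79% | −1 point |
| site variance share 0.15, medication shift 0.5 SD | 3.2% / 5.1% | 80% / 83% | +3 points |

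The plain test does not inflate type I error. It is conservative when the factors are strongly prognostic. Honouring the rule to the letter changes power very little.

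**4. Effect of ignoring the baseline score**

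Assumed, not from the documents: a 5-level score made by cutting a normal latent variable, 105 per arm, a latent shift of 0.35 SD, two-sided 5%. The comparison is a Mann-Whitney test on the follow-up score against a linear regression of that score on treatment and baseline score.

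| Latent correlation of baseline with follow-up | Mann-Whitney | Baseline-adjusted |
|---|---|---|
| 0 | about 66–68% | about the same |
| 0.5 | about 66–68% | about 77% |
| 0.7 | about 66–68% | about 87% |
| 0.8 | about 66–68% | about 95% |

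Type I error is near 5% for both methods.

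Plausibility check by formula, for an uncategorised normal outcome: z = 0.35 × √(105/2) = 2.54, so power = Φ(2.54 − 1.96) = 72%. With the rank test's efficiency of 0.955 on normal data, z = 2.54 × √0.955 = 2.48 and power is 70%. Baseline adjustment divides z by √(1 − ρ²):

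- ρ = 0.5: z = 2.54/0.866 = 2.93, power 83%
- ρ = 0.7: z = 2.54/0.714 = 3.55, power 94%
- ρ = 0.8: z = 2.54/0.6 = 4.23, power 99%

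The simulated values lie somewhat below these, as expected when both scores are cut to five levels.

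**5. Reading the two results together**

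Steps 3 and 4 use different sample sizes and shifts, so their power levels should not be compared with each other. Within each step the contrast is clear: the minimisation factors matter little, and the baseline score matters as soon as it correlates moderately with follow-up.

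**The case against.** **The rule the protocol breaks is not the source of the power loss.** This is right and it stands. The general rule names site and IPF medication, and those move power by −2 to +3 points. The larger gain comes from the baseline score, which the rule never mentions. The contradiction and the loss of precision are separate arguments for the same repair.

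**The missing baseline value is not peculiar to MRC and cough.** This also stands. The linear model for K-BILD names the minimisation variables but no baseline K-BILD value, so it cannot simply be copied as a baseline-adjusted model; the baseline has to be added.

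**A rank test is a standard choice.** It is. MRC is ordinal and a Visual Analogue Scale is bounded and often skewed. A reader might infer that the Mann-Whitney test is wrong or biased here; neither the text nor the calculation supports that.

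**A specific paragraph may override a general sentence.** Safety tables and microbiology are plainly descriptive and unadjusted, so the general sentence cannot cover everything. But MRC and cough are compared between arms with an effect size, a confidence interval and a p value. If an exception is meant, it should be stated.

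**The illustration rests on chosen inputs.** The 105 per arm is not in the document: 330/2 = 165, and the 264 of the Sample size section gives 132. The shift and the correlations are assumed too. The adjusted analysis simulated was a linear regression on the score, not the proportional-odds model recommended below. The figures show direction and rough scale only.

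**The trial may collect the LCQ.** A reader might infer that it does not, and that a listed outcome therefore has no data. That cannot be shown. The time and event schedule (Fig. 2) is not shown, part of the article was not available for review, and the article condenses a full protocol. What can be said is that no outcome section shown describes or defines it.

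**Conclusion.** The point holds as a minor one. The analysis section fixes an unadjusted test for two secondary outcomes directly after a rule that allows no exception, and the test leaves collected baseline scores unused. Type I error is not at risk and the primary analysis is untouched.

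The cost is precision. Under the stated assumptions, power of about 66–68% could be about 77% to 95% for baseline correlations of 0.5 to 0.8, and adjustment loses nothing if the correlation is zero. The textual conflict and the single undefined use of LCQ do not depend on any of these assumptions; the size of the gain does.

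**What to change.** - **MRC score:** a proportional-odds model with treatment, baseline MRC score, baseline licensed IPF medication and a random site effect, reported as a common odds ratio with its 95% confidence interval.
- **Cough:** name the Visual Analogue Scale in the analysis section, and use the linear model planned for K-BILD with the baseline cough value added.
- **Mann-Whitney:** keep it as a sensitivity analysis for both. If the investigators prefer it as the main analysis, state MRC and cough as an explicit exception to the adjustment rule. That removes the contradiction but not the loss of precision.
- **LCQ:** delete it, or define it among the outcomes with its visits.

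The cost is wording only: no new data and no change in sample size. The article says that analysis details are finalised before database lock, so the change can be made in that plan. The one statistical price is the proportional-odds assumption, which can be checked.
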